## Abstract

**Background:**

There is little scientific evidence to support the usual practice of providing outpatient rehabilitation to patients undergoing total knee replacement surgery (TKR) immediately after discharge from the orthopaedic ward. It is hypothesised that the lack of clinical benefit is due to the low exercise intensity tolerated at this time, with patients still recovering from the effects of major orthopaedic surgery. The aim of the proposed clinical trial is to investigate the clinical and cost effectiveness of a novel rehabilitation strategy, consisting of an initial home exercise programme followed, approximately six weeks later, by higher intensity outpatient exercise classes.

**Methods/Design:**

In this multicentre randomised controlled trial, 600 patients undergoing primary TKR will be recruited at the orthopaedic pre-admission clinic of 10 large public and private hospitals in Australia. There will be no change to the medical or rehabilitative care usually provided while the participant is admitted to the orthopaedic ward. After TKR, but prior to discharge from the orthopaedic ward, participants will be randomised to either the novel rehabilitation strategy or usual rehabilitative care as provided by the hospital or recommended by the orthopaedic surgeon. Outcomes assessments will be conducted at baseline (pre-admission clinic) and at 6 weeks, 6 months and 12 months following randomisation. The primary outcomes will be self-reported knee pain and physical function. Secondary outcomes include quality of life and objective measures of physical performance. Health economic data (health sector and community service utilisation, loss of productivity) will be recorded prospectively by participants in a patient diary. This patient cohort will also be followed-up annually for five years for knee pain, physical function and the need or actual incidence of further joint replacement surgery.

**Discussion:**

The results of this pragmatic clinical trial can be directly implemented into clinical practice. If beneficial, the novel rehabilitation strategy of utilising outpatient exercise classes during a later rehabilitation phase would provide a feasible and potentially cost-effective intervention to optimise the physical well-being of the large number of people undergoing TKR.

**Trial Registration:**

ACTRN12609000054213

## Background

The number of total knee replacements (TKR) performed each year is increasing rapidly in most developed countries [1-7]. In Australia, the total number of TKR operations performed has increased by 150% in the past decade [1]. Currently the mean age of patients undergoing TKR in Australia is 70 years, however the proportion of patients aged less than 65 years at the time of surgery has been increasing over the years reaching 32% in 2007 [1]. It is anticipated that the demand for TKR surgery will at least double again within the next decade and the average age at surgery will continue to decrease [3,8]. This trend is not only attributable to the aging of the population, increased prevalence of obesity and the expectation of a 'baby boomer' cohort less willing to accept the sedentary lifestyle, but also involves factors such as the evolution in implant design and surgical procedures resulting in better outcomes from TKR in relatively early stages of osteoarthritis (OA) [9]. It is readily apparent that the public health significance of TKR surgery is and will continue to be sizable.

Severe symptomatic knee OA is the main indication for almost all primary TKR surgery [1,6,9,10]. People affected by severe symptomatic knee OA experience significant functional limitation [11], and reduced lower limb muscle strength [12], aerobic fitness [13] and quality of life [14,15]. The need for rehabilitation following TKR is based on the contention that these deficits do not spontaneously resolve after surgery [16-19].

For the majority of patients, there are marked improvements after TKR in pain and physical function, with the maximum achievable benefit appearing around 6 months after surgery [20,21]. However, the magnitude of improvement is smaller than that demonstrated after total hip replacement surgery [21-23], and about 15% of patients still report moderate to severe pain a year after TKR despite no evidence of radiographic abnormalities [24]. Many years after TKR, patients are left with the lower limb muscle strength deficits evident prior to surgery [25-27] and with imbalances between knee extensor and flexor forces [25]. Poor ligamentous and neuromuscular control may result in destructive mechanical stresses and reduced control over anterior shear forces on the knee implant, potentially limiting implant longevity. It follows then, that muscle strengthening should be a major goal of rehabilitation. In support of this, achievement of greater knee extensor strength after TKR has been associated with improved physical function [26]. Younger people (<65 years of age) demonstrate less improvement after TKR [14] and have higher rates of revision surgery [10,28,29]. Effective rehabilitation may be particularly important in this younger group as they require prolonged implant longevity and are more likely to be in full-time employment or imposing greater physical demands on the knee implant.

In Australia, rehabilitation following TKR is mostly delivered in an outpatient setting by physiotherapists [30]. This rehabilitation commences immediately after discharge from the acute orthopaedic ward and is usually completed within 6 weeks, with resource-intensive one-on-one modes of delivery more common than class-based modes. However, evidence from randomised controlled trials suggests that such outpatient rehabilitation is no more effective than no treatment [31,32] or a home exercise programme [33,34]. One possible reason for the lack of demonstrable benefit is that the evaluated exercise programs did not specifically monitor or progress training intensity [31-34]. However training intensity is unlikely to be able to be progressed sufficiently to achieve meaningful changes in muscle strength in the first few weeks after TKR when patients are still experiencing the anaemia, pain and oedema inevitably associated with recovery from major orthopaedic surgery.

In support of our hypothesis, a recent trial provided initial evidence that a supervised exercise programme commencing two months after TKR resulted in improved function and reduced pain compared to a home exercise programme [35]. The clinical benefits were evident both at the end of the treatment period and six months after TKR. Apart from timing, another noticeable difference between this rehabilitation programme and those evaluated in other clinical trials was that the training intensity was closely monitored and each exercise had varying difficulty and complexity to allow progression. However, the rehabilitation programme was delivered on an individual basis so was resource-intensive.

The aim of the proposed clinical trial is to compare, the long-term effectiveness of a novel rehabilitation strategy versus current usual rehabilitative care received after discharge from the orthopaedic ward in patients who have undergone primary TKR. The novel rehabilitation strategy consists of an initial home exercise programme during the early recovery period followed by two months of outpatient exercise classes. A health economic evaluation, undertaken from the perspectives of the health sector and society, will be conducted alongside this clinical trial. We hypothesise that the novel rehabilitation strategy will lead to greater gains in physical well-being and be more cost-effective than usual care.

## Methods

The MARKER (Maximum Recovery after Knee Replacement) Study is a multicentre randomised controlled trial that will be conducted in 10 large public and private hospitals in Australia. Participants will be required to provide written informed consent prior to starting the study. Ethics approval has been obtained from the University of Sydney Human Research Ethics Committee and from the Ethics Review Committee (RPAH Zone) of the Sydney South West Area Health Service using the National Ethics Application Form . The MARKER Study has been registered at the Australian and New Zealand Clinical Trials Registry (ACTRN12609000054213).

Potential participants will be screened and recruited at the orthopaedic pre-admission clinic. Inclusion criteria are: (i) aged between 45 to 74 years, (ii) planned unilateral or bilateral primary TKR, and (iii) able to be discharged home from the orthopaedic ward. Exclusion criteria include: (i) previous unicompartmental replacement or tibial osteotomy on the same knee, (ii) previous lower limb joint replacement surgery within the last six months, (iii) further lower limb joint replacement surgery anticipated within the next 12 months, (iv) major co-morbidity precluding aerobic exercise at 50–60% maximum heart rate, (v) rheumatoid arthritis, (vi) major neurological conditions, or (vii) inability to return to one of the participating sites for outpatient exercise classes.

There will be no change to usual medical or rehabilitative care during the peri-operative inpatient period. After TKR, but before discharge from the orthopaedic ward, participants will be randomly allocated to either the novel rehabilitation strategy or usual rehabilitative care specific for the orthopaedic centre or surgeon (control group). The randomisation schedule will be generated a priori using a computer generated random number sequence by an independent researcher with no participant contact, in varying blocks of four or six, and stratified by recruitment site and by unilateral or bilateral TKR. Allocations will be sealed in opaque and consecutively numbered envelopes with a clear audit trail.

### Interventions

#### Novel rehabilitation strategy

Stage 1: Initial home exercise programme (usually Week 1 to 6 after randomisation)

Participants will be provided with a written home exercise programme on discharge from acute care (Additional file 1). The exercises will focus on maintaining and improving active knee flexion and extension range of motion. Participants will repeat the exercises 5 to 10 times per exercise, three times daily. Participants' progress, including adherence to the home exercise programme, walking ability and knee symptoms (e.g. pain, wound healing, range of motion, swelling), will be monitored weekly by a research physiotherapist, with clinic visits in the first one or two weeks and by telephone calls thereafter.

Stage 2: Outpatient exercise classes (usually Week 6 to 14 after randomisation)

Approximately five weeks after randomisation, the research physiotherapist will commence screening during the weekly telephone calls to assess eligibility to commence the classes: (i) surgical wound healed, (ii) full weight-bearing tolerated on the operated limb, (iii) ambulating independently outdoors for more than 50 m, and (iv) not requiring daily opioid-based analgesics for knee pain. Participants will join the outpatient exercise classes as they become eligible.

The classes will be circuit-based and supervised by a physiotherapist. The one hour classes will be conducted twice a week. Participants will be encouraged to attend the ongoing classes for eight weeks. Each class will consist of a short warm up and cool down component, progressive functional and strengthening exercises, and a 20-minute monitored aerobic exercise session on a stationary bicycle (Additional file 1). In order to standardise this programme across centres, minimal equipment will be used and supervising physiotherapists will receive prior training from research staff as well as a written manual of procedures. Participants will record the loads, repetitions and sets for to each functional and strengthening exercise they complete, and the duration and exertion (maximal heart rate or the Borg Rating of Perceived Exertion Scale [36]) for the aerobic exercise, in an exercise diary during the classes.

At the beginning of each exercise class, knee pain, range of motion and swelling will be evaluated to allow appropriate exercise progression. To allow this level of monitoring, class size will be restricted to a maximum of six participants. An education class will be provided once a month focusing on the rationale for increasing lower limb muscle strength and beneficial lifestyle behaviours appropriate after TKR. In addition, participants will be required to do at least one additional intensive exercise session per week at home, consisting of 30 minutes of walking outdoors or stationary bicycle.

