### Sample size

Based on preliminary data [35], a sample size of 600 participants will be required. This sample size will provide 80% power of detecting a 15% difference in the proportion of treatment responders (OMERACT-OARSI responder criteria [45]) between the groups, and allows for up to 10% cross-over of treatment allocation and a 15% loss to follow-up [61]. In addition, this sample size will provide more than 90% power to detect clinically significant differences in each of the continuous secondary outcome measures.

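### The novel arm is treated in physiotherapist-led classes, but the stated sample size and the ANOVA for the WOMAC primaries make no provision for clustering by physiotherapist or class

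*Protocol article*

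**What the plan says.** All places are in the Protocol article.

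- **Novel rehabilitation strategy.** After a home programme, the novel arm attends group sessions twice a week for eight weeks, usually in weeks 6 to 14: "The classes will be circuit-based and supervised by a physiotherapist", and "class size will be restricted to a maximum of six participants". Symptoms are checked at the start of each class to guide progression. Entry is rolling: "Participants will join the outpatient exercise classes as they become eligible". Supervisors are trained and given a manual so that delivery is alike across centres.
- **Control group.** Usual care is expected to be given mostly by a physiotherapist to one patient at a time.
- **Methods.** There are 10 hospitals. Randomisation is in blocks of four or six, stratified by recruitment site and by unilateral or bilateral surgery.
- **Sample size.** "This sample size will provide 80% power of detecting a 15% difference in the proportion of treatment responders", and the figure "allows for up to 10% cross-over of treatment allocation and a 15% loss to follow-up". No ICC, cluster size or design effect is mentioned.
- **Statistical analysis.** Continuous outcomes, which include both WOMAC primaries, get a two-way repeated measures ANOVA of group and follow-up time. Dichotomous outcomes get generalised estimating equations (GEE) or a linear mixed model. Neither description names a site, physiotherapist or class term.

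**The concern.** Patients who share a supervising physiotherapist, or who train together, may end up more alike than patients who do not. Here that sharing is built into the component that the trial is meant to test, and it arises mainly in one arm. An analysis that treats novel-arm patients as independent then understates the variance of the novel-arm mean. Confidence intervals for the treatment effect come out too narrow, and the type I error rate exceeds its nominal level. A sample size worked out for independent patients also delivers less power than it appears to.

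This goes beyond detail that an article may leave to a fuller document. The article lists its sample-size allowances and fixes the method for the continuous primaries, and that method as described has nowhere to put the correlation.

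**Working it through.** **Inputs from the article:** 600 participants, 10 sites, 15% loss, 10% cross-over, a 15-point difference in responders (read as absolute), 80% power, at most six per class.

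**Assumed, because not stated:** 1:1 allocation, two-sided 5% test, equal site sizes, ICC of 0.01, 0.02 or 0.05 in the novel arm and zero in the control arm.

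**Step 1. Can 600 be reproduced without clustering?** Not uniquely, because the control rate, alpha and direction of cross-over are missing. But it can be reached. For 30% v 45%, the two-proportion formula without continuity correction gives 163 per arm. Cross-over of 10% in both directions shrinks the difference by the factor 1 − 2 × 0.10 = 0.8. Then 163 / 0.8² = 254.7, and 254.7 / 0.85 = 299.6, so 300 per arm and 600 in all. No clustering allowance is needed to arrive there. With one-way cross-over the largest requirement over the control rates tried (20% to 80%) is at 42.5% v 57.5%: 174 / 0.9² / 0.85 = 252.7, so 506 in all (544 with continuity correction). In that case 600 carries slack.

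**Step 2. Cluster sizes.** Two cases bracket the question.

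- *m = 6:* the session cap. Entry is rolling, so this illustrates a small cluster and is not the documented cluster size.
- *m = 25.5:* 300 / 10 = 30 novel-arm patients per site, × 0.85 = 25.5 evaluable. This is the upper end, with one physiotherapist running all classes at a site.

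**Step 3. Inflation.** Novel-arm design effect DE = 1 + (m − 1) × ICC. Average variance inflation A = (1 + DE)/2. The true standard error is √A times the naive one. Actual error of a nominal 5% test = 2[1 − Φ(1.96/√A)]. A nominal 80% power becomes Φ(2.80/√A − 1.96). Equivalent total N = 600 × A, rounded up.

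| m | ICC | DE | A | √A | Actual error | Nominal 80% becomes | Equivalent N |
|---|---|---|---|---|---|---|---|
| 6 | 0.01 | 1.05 | 1.025 | 1.012 | 5.3% | 79% | 615 |
| 6 | 0.02 | 1.10 | 1.050 | 1.025 | 5.6% | 78% | 630 |
| 6 | 0.05 | 1.25 | 1.125 | 1.061 | 6.5% | 75% | 675 |
| 25.5 | 0.01 | 1.245 | 1.1225 | 1.059 | 6.4% | 75% | 674 |
| 25.5 | 0.02 | 1.49 | 1.245 | 1.116 | 7.9% | 71% | 747 |
| 25.5 | 0.05 | 2.225 | 1.6125 | 1.270 | 12.3% | 60% | 968 |

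These are normal approximations. They ignore the further penalty from having few clusters.

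**Step 4. Is 80% missed?** Take 255 evaluable per arm and 42.5% v 57.5% before cross-over. One-way cross-over leaves 42.5% v 56%, and two-way leaves 44% v 56%. The novel-arm variance is multiplied by DE.

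| Case | One-way cross-over | Two-way cross-over |
|---|---|---|
| No clustering | 86.4% | 77.5% |
| m = 6, ICC 0.01 / 0.02 / 0.05 | 85.6 / 84.7 / 82.2% | 76.5 / 75.5 / 72.6% |
| m = 25.5, ICC 0.01 / 0.02 / 0.05 | 82.3 / 78.2 / 67.2% | 72.6 / 68.2 / 57.0% |

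The answer turns on inputs that the article does not give.

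**The case against.** Several points on the other side stand.

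- **No ICC or cluster size is documented.** Six is a cap per session, and the number of physiotherapists per site is not given. Training and a manual may keep the ICC low. At six per cluster the effect is modest.
- **The responder model may already cope.** A reader might infer that the GEE or mixed model treats the participant as the only cluster. The article does not say so: it names no unit, either model could carry a physiotherapist or class level, and the full protocol or SAP is not shown.
- **Site correlation is a separate matter.** A reader might count everything that patients at a site share. But randomisation is stratified by site, so site effects common to both arms cancel from the comparison. Leaving them out of the model tends to make standard errors too large, which works against the effect described here. Only variation specific to the novel arm counts, and the figures above are for that alone.
- **Controls may be clustered too.** Patients seen one at a time can still share a physiotherapist. Zero correlation in the control arm is an assumption.
- **The 6-week assessment largely precedes the classes**, so it is hardly affected.

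What these points do not remove is that the ANOVA set out for the WOMAC primaries has no place for a physiotherapist or class effect. Stratification by site does not balance an effect that exists only in the novel arm.

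**Conclusion.** The point holds in conditional form. The design is partially nested, no allowance is stated, and the method named for the continuous primaries cannot represent it. Any positive novel-arm correlation adds variance to the 6- and 12-month treatment effects that this method leaves out. For assumed ICCs of 0.01 to 0.05 the consequence runs from negligible (5.3% error with six per cluster) to serious (12.3% error with one physiotherapist per site).

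A reader might go further and infer that the trial is underpowered against its stated 80%. The article does not support that. With one-way cross-over, 600 has slack and still gives about 82% at six per cluster and ICC 0.05. With two-way cross-over at the same response rates, power is 77.5% before any clustering is counted. Without the control rate, alpha and cross-over direction, a shortfall due to clustering can be neither shown nor excluded.

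**What to change.** 1. Record the supervising physiotherapist (and class) for every novel-arm participant. This is one data field, and it may be hard to recover if it is not captured during delivery.
2. Analyse the 6- and 12-month primary outcomes with a mixed model that includes randomisation site and a physiotherapist or class random effect in the novel arm only, with small-sample degrees of freedom. At the least, pre-specify this as a sensitivity analysis. For responders, name the cluster level that the GEE or mixed model will use.
3. Restate the power in the Sample size section over a range of ICCs and cluster sizes, with the control rate, alpha and direction of cross-over given.

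The cost is some analysis text, the extra field, wider intervals and a less favourable power figure. Intervals widen by about 1% to 6% at six per cluster, and by up to about 27% at 25.5 per cluster with ICC 0.05. No change to how treatment is delivered is needed.

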#### Control group

Participants in the control group will receive the usual rehabilitation management as recommended by their orthopaedic surgeon or provided by the hospital, and can be delivered in the inpatient or outpatient setting. Findings from a previous Australian national survey demonstrate that rehabilitation will usually commence immediately after discharge from the orthopaedic ward, be completed within 6 to 8 weeks after TKR and will be provided on an individual basis by a physiotherapist in the outpatient setting [30]. Rehabilitation received by the control group will be documented in the patient diary.

### Outcomes assessments

Assessments will be conducted at baseline (pre-admission clinic), and 6 weeks, 6 months and 12 months after randomisation by assessors blinded to treatment allocation. Demographic information collected at baseline will include height, weight, socioeconomic data (highest level of education completed, health insurance status, employment status, occupation), history of lower limb arthritis and joint surgery and the 19-item Hospital for Special Surgery Knee Replacement Expectations Survey [37,38]. This survey has been tested for internal consistency (Cronbach's alpha = 0.77) and test-retest reliability [37].

#### Primary outcomes

The primary outcomes will be self-reported knee pain and physical function measured on the Western Ontario and McMaster Universities (WOMAC) Osteoarthritis Index, using a 5-point Likert scale (WOMAC LK3.1) [39]. The WOMAC consists of 24 items covering three subscales: pain (five items), stiffness (two items) and physical function (17 items). The pain and physical function subscale will be used, each subscale transformed to a score ranging from 0 (no pain or difficulty) to 100 (maximum pain or difficulty). The WOMAC is a widely-used questionnaire specifically designed to evaluate knee and hip OA [40,41]. Its clinimetric properties have also been validated in patients undergoing TKR [42-44].

Responses on the WOMAC will also be dichotomised according to the OMERACT-OARSI responder criteria for OA [45], i.e. treatment responders are defined as those participants achieving ≥20% improvement in both pain and physical function scores and an absolute change of ≥10, or ≥50% improvement in pain or physical function scores and an absolute change of ≥20 on the WOMAC.

